## Abstract

**Background:**

Multiple Sclerosis (MS) causes many different symptoms, with some of the most dominant being impaired balance and walking performance. Exercise effectively improves strength, balance, and walking performance, but barriers to performing exercise, such as fatigue and logistical issues, do exist. A potential strategy to overcome these barriers is the use of telerehabilitation, which has shown promising results. Few previous studies have measured strength, balance, and walking outcomes, and none have used systems that provided real-time feedback. Therefore, the present study aims to compare telerehabilitation to a paper-based home-based exercise program to evaluate the effectiveness on strength, balance, and walking outcomes. The telehealth intervention will be delivered through an innovative platform that uses Artificial Intelligence algorithms to provide users and clinicians with tailored feedback on performance and adherence.

**Methods:**

This study is a multinational, feasibility, pilot randomised controlled trial investigating the effects of an AI-based telerehabilitation intervention in persons with multiple sclerosis (pwMS). Participants (n = 96) will be randomised to receive either 10 weeks of a home-based AI telerehabilitation intervention or a home-based exercise intervention with paper-based instructions. The primary clinical outcome is the 30-second sit-to-stand test (30STS), and secondary clinical outcomes are balance, fatigue, MS impact, quality of life, symptoms of anxiety and depression, and cost-effectiveness analyses. Feasibility, in terms of recruitment and retention, the acceptability of procedures, and compliance and adherence, will also be captured.

**Trial registration:**

ClinicalTrials.gov NCT07310914

## 1. Introduction

Multiple Sclerosis (MS) is an autoimmune, neurodegenerative disease in the central nervous system [1], affecting over 2.8 million people worldwide [2]. Many symptoms can occur during the disease course, but some of the most debilitating symptoms, according to people with MS (pwMS) themselves, are impaired lower limb strength, balance, and mobility [3,4]. Also, up to 85–90% of pwMS experience impaired balance and walking performance throughout the disease course, making these persistent symptoms [5,6]. Hence, treatments to improve lower limb strength, balance, and walking performance are highly warranted, with exercise proven to be highly effective [7].

Exercise can be conducted in various settings (supervised/unsupervised, gym-based/home-based, etc.), with supervised exercise programs at a clinic considered the most optimal and effective [8]. However, a lack of access to these programs, for instance, for those living in remote areas or where healthcare/medical facilities are available but no MS experts are present, may make it difficult to engage in optimal exercise programs [9]. In a recent survey of 741 pwMS, travel and/or moving issues were the second-largest barrier to practice exercise, behind fatigue [10].

A potential way to overcome this barrier to exercise is telerehabilitation (TR), which can be defined as “*the application of information and communications technology to deliver rehabilitation services over a distance by linking a healthcare provider to a beneficiary, caregiver, or any persons (s) responsible for delivering care to the beneficiary, for screening, assessment, intervention, consultation/coaching and/or supervision/monitoring.”* [11]

Interestingly, TR, as a concept, appears effective at improving key symptoms frequently reported by pwMS, including impaired mobility and walking performance [12,13] and impaired balance [13,14].

When focusing only on exercise-based TR, a systematic review and meta-analysis including 14 RCTs found it beneficial for fatigue, depression, and overall quality of life [15]. However, beneficial effects on balance, mobility, and walking performance were less robust and convincing.

In another systematic review investigating the effects of TR on quality of life in pwMS, TR was found to be more effective than no intervention and as effective as in-person treatment [16]. The review included 12 randomized controlled trials (RCTs), with different types of TR interventions (4 video-based interventions, 3 app-based interventions, 2 augmented reality interventions, 1 virtual reality intervention, 1 video-based intervention with focus on motor imagery, along with an app, and 1 study did not define their TR). Of the studies included, 4 had an exercise component (according to the definition by Caspersen et al. [17]) in their interventions, including pelvic floor muscle training [18,19], resistance and balance training [20], or Pilates [21].

However, despite the numerous potential benefits of TR, several limitations, such as the need for specialist equipment, complex technical solutions, technical difficulties, and lack of digital literacy, may currently prevent its widespread adoption in the MS population. Furthermore, most studies conducted have relatively small sample sizes, do not provide direct feedback to participants, and mainly report patient outcomes, with few investigating lower limb strength, balance, and walking outcomes [22].

A potential way to provide direct feedback to participants is to use a platform that applies artificial intelligence (AI). The platform (WizeCare™) used in the present study can be accessed on either a phone or a computer, with no other devices required. The platform allows direct contact between the participant and therapist using the devices’ built-in cameras. Furthermore, it will use AI software to provide direct feedback to the participant and will allow the therapist to continuously monitor adherence and compliance to the program, as well as movement quality.

Therefore, we aim to examine feasibility and preliminary effectiveness in a multinational, pilot RCT trial comparing AI TR with a paper-based, home-based exercise program. We hypothesize that the AI TR program will be superior to the paper-based exercise program in improving performance on the 30 STS test. Additionally, the RCT will include an economic evaluation to determine the cost-effectiveness of the TR system.

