### 2.7. Outcomes

The ***primary clinical outcome*** of the trial is lower-limb functional performance, assessed using the 30-Second Sit-to-Stand Test (30STS). This test was selected as it represents a weight-bearing activity relying on balance, coordination, and muscle strength/power (predominantly lower extremity). Moreover, the majority of exercises in the trial target lower-limb muscle groups similarly. During the 30STS, participants rise from a standard chair without armrests as many times as possible within 30 seconds, with the total number of repetitions recorded as the score. The 30STS has demonstrated strong validity and reliability in pwMS [29]. The primary outcome will be assessed at baseline (T0) and at the end of the 10-week intervention period (T1).

To characterize the study sample, a set of descriptive and clinical measures will be collected at T0, including sex, age, height, body mass, time since MS diagnosis, MS subtype (i.e., relapsing–remitting, secondary progressive, or primary progressive), medication use, comorbidities, disability status (EDSS or PDDS), and use of walking aids (cane, crutches, or rollator). Digital literacy will also be assessed at baseline using the Digital Literacy Scale [30].

***Secondary clinical outcomes*** will be assessed at T0 and T1. Mobility and balance will be evaluated using the Short Physical Performance Battery (SPPB), consisting of standing balance tests, walking speed, and repeated chair rises [31,32], the MiniBESTest [33–35], and the Functional Reach Test (FRT) [36,37]. Walking performance will be measured using the Timed 25-Foot Walk Test (T25FWT) [38,39] and the Six-Minute Walk Test (6MWT) [40]. Cognitive function will be assessed with the Symbol Digit Modalities Test (SDMT) [41].

A range of patient-reported outcomes will be collected at both T0 and T1. These include the MSIS-29 for the physical and psychological impact of MS [42], the Modified Fatigue Impact Scale (MFIS) for fatigue [43], the Multiple Sclerosis Walking Scale–12 (MSWS-12) for perceived walking limitations [44], the State-Trait Anxiety Inventory (STAI) for anxiety [45], the Quick Inventory of Depressive Symptomatology (QIDS) for depressive symptoms [46], and the EQ-5D-5L for health-related quality of life [47]. All participants will complete a semi-structured interview exploring usability, satisfaction, and experiences with the trial process, providing qualitative insights that complement the quantitative outcomes.

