An ***economic evaluation*** will be performed from both health-system and societal perspectives. The economic evaluation methodology, data collection procedures, and resource-use measures were developed with input and guidance from a health economics expert within the PLATINUMS consortium to ensure the appropriateness of the proposed approach. Participant-level resource use, including healthcare and social care contacts, informal caregiving, productivity loss, medication use, assistive devices, and out-of-pocket expenses, will be assessed using an adapted Client Service Receipt Inventory (CSRI) [48]. Provider and system-level costs (e.g., platform setup, operational resources, staff training, therapist time, clinical space, administrative support, printed materials) will be captured using standardized implementation cost forms. Quality-adjusted life years (QALYs) will be derived from EQ-5D utilities using the area-under-the-curve method, and costs and QALYs will be compared between study arms to compute the Incremental Cost-Effectiveness Ratio (ICER) [49].

Feasibility of the trial. To assess the feasibility, we will evaluate 1) recruitment and retention rates, 2) evaluation of data collection procedures, 3) evaluation of acceptability of the interventions and study procedures, 4) evaluation of the ability of the consortium to manage the study, 5) safety of the interventions, and 6) preliminary measures of effectiveness of participant responses to the intervention.

When evaluating recruitment rates, we will determine whether 8 months is an acceptable time frame for recruiting 96 participants across 4 sites. To evaluate the data collection and intervention procedures, our semi-structured interviews with participants in each country will help us determine them. For the intervention’s acceptability, we consider an 85% retention rate acceptable and will explore this further in the semi-structured interviews. Furthermore, we will use the Telehealth Usability Questionnaire (TUQ) [50] to assess the usability of the TR system. Trial management will be overseen by an external advisory board. Adverse events (AEs) will be closely monitored throughout the study period, and rates will be compared with those in other exercise intervention studies [51].

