### 2.9. Sample size

As this study is a pilot feasibility RCT, one aim is to assess feasibility, refine study procedures, and obtain preliminary estimates of variability to inform sample size for a future definitive RCT. Accordingly, the sample size is based on methodological guidance for pilot studies rather than on a formal power calculation. Following the stepped rule-of-thumb proposed by Whitehead et al.[54], approximately 12 participants per arm (i.e., 24 participants in total) are recommended for early-stage pilot trials with continuous outcomes and small to medium expected effect sizes. In line with this guidance, 24 participants per country (a total of 96) will be recruited for the study. If needed, data can be analyzed separately by country. This sample size is expected to provide sufficient information on feasibility metrics, acceptability of study procedures, and change in the primary outcome.

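### The economic aim is to determine cost-effectiveness, but a 10-week, two-point, unpowered ICER can give only a preliminary within-trial estimate

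*Protocol article*

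**What the plan says.** The last paragraph of section 1 (Introduction) sets the economic aim without qualification: "the RCT will include an economic evaluation to determine the cost-effectiveness of the TR system". The same paragraph words the clinical aim more modestly, as feasibility and preliminary effectiveness.

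Section 2.7 (Outcomes) gives the ingredients:

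- **Utility data.** "A range of patient-reported outcomes will be collected at both T0 and T1", and EQ-5D-5L is on that list. T1 is defined under the primary outcome as falling "at the end of the 10-week intervention period (T1").
- **QALYs.** "Quality-adjusted life years (QALYs) will be derived from EQ-5D utilities using the area-under-the-curve method".
- **Costs.** "Provider and system-level costs (e.g., platform setup, operational resources, staff training, therapist time, clinical space, administrative support, printed materials) will be captured" on standard forms, alongside participant-level resource use.
- **Result.** "costs and QALYs will be compared between study arms to compute the Incremental Cost-Effectiveness Ratio (ICER").

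Section 2.9 says that "24 participants per country (a total of 96) will be recruited for the study", from a pilot rule of thumb and without a formal power calculation. Strengths and Limitations in section 3 says that the trial lacks power for efficacy and promises caution about clinical trends. It attaches no such limit to the economic result.

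**The concern.** The strongest verb in the aims is attached to one of the least well-supported quantities. An ICER is a ratio of two estimated differences. Here its denominator is a QALY difference accumulated over 10 weeks from two measurements per person, in a sample not sized for it. When that denominator is small relative to its standard error, the ratio can swing widely or change sign.

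The article mentions no utility measurement after T1, no extrapolation and no decision model. A fuller health-economics plan could add modelling, but it could not supply utilities that were never collected. If the stated aim is followed, the report will present a 10-week ratio as an answer on whether the system is cost-effective, and nothing in the limitations paragraph tells the reader otherwise.

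**Working it through.** **Inputs from the protocol article.** 12 per arm, 24 per country and 96 in total (2.9); 1:1 allocation (2.5); T1 at 10 weeks and 85% retention regarded as acceptable (2.7).

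**Assumptions, not in the article.** Between-arm utility difference at T1, *d*: 0.05, range 0.02 to 0.10. SD of T1 utility after baseline adjustment: 0.10 to 0.20. Linear change between T0 and T1. Cost and useful-life values are illustrative.

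**Step 1. The plan's own figure.** 12 × 2 × 4 = 96, which reproduces the stated total. That is 48 per arm, and 48 × 0.85 = 40.8, about 41 per arm with T1 data.

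**Step 2. QALY gain.** Two-point area under the curve, no baseline difference: 0.5 × *d* × 10/52.

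| *d* | QALY gain at 10 weeks |
|---|---|
| 0.02 | 0.0019 |
| 0.05 | 0.0048 |
| 0.10 | 0.0096 |

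**Step 3. Precision.** SE = 0.5 × (10/52) × SD × √(2/41), with √(2/41) = 0.2209.

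| SD | SE | 95% half-width (1.96 × SE) | Power at *d* = 0.05 |
|---|---|---|---|
| 0.10 | 0.0021 | 0.0042 | about 62% |
| 0.15 | 0.0032 | 0.0062 | about 33% |
| 0.20 | 0.0042 | 0.0083 | about 20% |

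For *d* = 0.05, an interval centred on the assumed gain runs from 0.0006 to 0.0090 at SD 0.10, and from −0.0035 to 0.0131 at SD 0.20. It crosses zero once the SD exceeds 0.05/(1.96 × 0.2209), about 0.116. For *d* = 0.02 it crosses zero throughout the SD range. For *d* = 0.10 it excludes zero throughout.

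**Step 4. Effect on the ratio.** Take an incremental cost of 100 currency units per participant, treated as known. At *d* = 0.05 and SD 0.10, the ICER is 100/0.00481, about 20,800 per QALY. At the two ends of the QALY interval it is 100/0.00897, about 11,100, and 100/0.00065, about 155,000. At SD 0.20 the interval includes zero and the ratio has no finite bound. Uncertainty in cost would add to this.

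**Step 5. Sensitivity to horizon.** If the gain held to week 52, the QALY gain would be *d* × (5 + 42)/52, which is 47/5 = 9.4 times the 10-week figure for any *d*. If it faded linearly to zero at week 52, it would be *d* × (5 + 21)/52, or 5.2 times. If it vanished at week 10, the factor would be 1. The trial cannot distinguish these cases.

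**Step 6. Sensitivity to cost apportionment.** Suppose a fixed cost of 10,000 for the TR arm, or 10,000/48 = 208 per participant. At *d* = 0.05, full charging adds 208/0.00481, about 43,300 per QALY. Straight-line spreading over 5 years, with only the 10-week share charged, multiplies this by (10/52)/5 = 1/26, giving about 1,700. These are two ends of a rule that the article does not state. Neither is shown to be planned.

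**The case against.** The best case for the plan is that a within-trial ICER from area-under-the-curve QALYs is a conventional analysis, that the half-weighting of a T1 gain is simply what linear interpolation gives, and that the whole paper is framed as a pilot. The methods were also developed with health-economics input, and an article leaves costing detail to a fuller plan. All of that stands as a defence of the calculation. It does not defend the aim as worded, because the pilot caution in section 3 covers clinical trends and not the economic conclusion.

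Three stronger readings are tempting, and the documents support none of them.

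- **That set-up and training costs enter the ICER in full as one-off charges on TR.** Section 2.7 says only that they are captured. It does not call them one-off and gives no allocation rule, a detail that an article commonly leaves out. Section 2.6 describes a commercially available platform, so its cost may be a fee. It also says that all physiotherapists are trained, so part of the training cost may fall on both arms and cancel.
- **That the ICER will inform whether to proceed.** The numerical criteria in 2.7 are retention, adherence and compliance. Cost-effectiveness is not among the six feasibility items. Section 2.12 has the patient panels discuss feasibility and effectiveness and whether to proceed, and does not mention an ICER.
- **That the ICER would not reflect the value of TR.** This presumes that benefit persists beyond week 10. The article gives no evidence either way, and if the effect faded at once the 10-week figure would lose little.

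**Conclusion.** The point holds for the stated aim. A design that ends at 10 weeks, with two EQ-5D-5L measurements and no power calculation, cannot determine the cost-effectiveness of the TR system, and the Introduction says that it will. That conclusion rests on the article's own text and needs no assumed value.

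The size rests on assumptions. At a utility gain of 0.05, the QALY difference is about 0.005 with a half-width of about 0.004 to 0.008. Only a large gain would give a clearly positive denominator across the assumed SD range. The ratio would also move several-fold with horizon and cost apportionment. The absence of an apportionment rule is context for that sensitivity and not itself an error. This should be corrected, but it concerns the claim made for the analysis and leaves the analysis itself feasible.

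**What to change.** **Section 1.** Replace the aim of determining cost-effectiveness with testing the collection of cost and EQ-5D-5L data and giving a preliminary 10-week within-trial estimate.

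**Section 2.7.** Report incremental costs and incremental QALYs separately, each with an interval. As a sensitivity analysis, show results with and without platform set-up and training costs. Label any ICER as a 10-week within-trial figure that does not establish cost-effectiveness.

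**Cost.** This is a wording change and a little more analysis of data already to be collected, with no added visits, measures or participants. The price is a more modest economic claim. Section 2.14 says that recruitment has not begun, so the change can be made before any data exist.

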## 2. Materials and methods

### 2.1. Trial design

This will be a single-blind, 1:1 parallel-group, multicentre, pilot feasibility randomized controlled trial. The study protocol has been reported using the Standard Protocol Items: Recommendations for Interventional Trials (SPIRIT) statement guidelines [23], and the associated publication will be reported in accordance with the CONsolidated Standards of Reporting Trials (CONSORT) extension for randomized pilot and feasibility trials [24].

### 2.2. Trial setting

This multinational study will be conducted in Israel, Italy, Ireland, and Denmark. In Israel, it will take place at the Sheba Multiple Sclerosis Center in Tel Hashomer; in Italy, at the Regional Multiple Sclerosis Center of Sardinia (ASL Cagliari); in Ireland, at the MS Society of Ireland, Dublin; and in Denmark, at the Danish MS Hospitals in Ry and Haslev.

### 2.3. Eligibility criteria

*Inclusion criteria*

Participants must meet all the following criteria to be eligible for the study:

[a] Age 18 years or older.[b] Definite diagnosis of multiple sclerosis (MS) according to the McDonald criteria [25] (including both relapsing–remitting and progressive forms).[d] Expanded Disability Status Scale (EDSS) score between 2.5 and 6.5, or Patient Determined Disability Score (PDDS) between 2 and 6, corresponding to deficits in lower-limb functional performance[e] Preserved ambulatory function, defined as the ability to walk at least 20 meters independently, with or without an assistive device.[f] Willingness and ability to travel to the local study site for evaluation sessions.[g] Access to an internet-enabled platform suitable for study participation.

*Exclusion criteria*

[a] Presence of comorbidities that may hinder safe participation in the study.[b] Documented MS relapse and/or corticosteroid treatment within the past three months.[c] Severe cognitive impairment that prevents following simple instructions or providing informed consent.

### 2.4 Recruitment

Participants will be recruited through specialized inpatient and outpatient MS clinics and via social media platforms commonly used by pwMS. Prior to enrolment, potential participants will undergo an in-person screening to determine eligibility based on the study’s inclusion and exclusion criteria. Eligible individuals will receive oral information about the study and will be allowed to ask questions. In addition, they will be provided with two information leaflets: one describing the study’s rationale, design, and objectives, and another outlining their rights as participants in a health science research project.

### 2.5. Randomization

Participants who meet all eligibility criteria and complete the baseline evaluation will be randomly assigned at each site in a 1:1 ratio to either the TR intervention group or the paper-based exercise group. A computer-generated randomization sequence stratified by study site will be used. Randomization procedures at all sites will be coordinated according to a common study protocol developed by the project team. Allocation concealment will be ensured using sequentially numbered, opaque, sealed envelopes prepared and maintained locally at each participating site. Envelopes will be opened only after eligibility has been confirmed and baseline assessments have been completed.

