#### Statistical Analysis Plan.

Feasibility outcomes, including recruitment rate, retention rate, adherence, compliance, acceptability, and adverse events, will be summarized using descriptive statistics. Continuous variables will be reported as means and standard deviations or medians and interquartile ranges, as appropriate, while categorical variables will be reported as frequencies and percentages. These outcomes will be used to assess the feasibility of conducting a future definitive trial.

Baseline demographic and clinical characteristics will be summarized using appropriate descriptive statistics. Variables with a normal distribution will be reported as mean and standard deviation, while non-normally distributed variables will be summarized as median and interquartile range. To examine changes in outcomes from baseline to the end of the intervention period, a multivariate repeated-measures mixed-effects regression model will be applied. Participant ID will be included as a random effect, and group (intervention vs. comparator) and time (T0 vs. T1) will be included as fixed effects. The model’s assumptions, including normality of residuals and homogeneity of variance, will be assessed using graphical and statistical methods. If these assumptions are not met, appropriate data transformations, non-parametric methods, or other alternative statistical approaches will be considered.

The primary analysis will adhere to the intention-to-treat principle, ensuring that all randomized participants are analyzed in the groups to which they were originally assigned, irrespective of adherence or protocol deviations. A secondary per-protocol analysis will be conducted, including participants who complete the post-intervention assessment and meet the predefined adherence (≥80%) and compliance (≥75%) criteria. Sensitivity analyses will be performed to assess the impact of missing outcome data and to compare findings obtained from the intention-to-treat and per-protocol populations. Robustness will be evaluated by examining whether the overall direction and interpretation of the results remain consistent across these analyses.

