### Operational Considerations, Amendments, and Dissemination

Because this study involves sites from different countries and operational systems, differences in site logistics, staffing, and local clinical practices may influence recruitment rates and adherence, and hence each country has sufficient numbers for its own pilot study analysis. Standardized training and regular cross-site communication will be used to minimize variability. Any protocol amendments will require approval from the consortium, the advisory board of three MS rehabilitation experts, and all relevant institutional ethics committees. The study may be paused or terminated if major unforeseen safety or operational concerns arise.

Findings from this feasibility trial will inform the design of a future fully powered RCT. Regardless of outcome (positive, negative, or neutral), results will be disseminated through peer-reviewed publications, conference presentations, and patient-focused communication materials co-created with patient panels at each site.

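### Randomisation is stratified by site but the stated model has no site term; the cost is nil to modest, depending on which contrast is tested

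*Protocol article*

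**What the plan says.** On the design, section 2.5 states that participants "will be randomly assigned at each site in a 1:1 ratio" and that "A computer-generated randomization sequence stratified by study site will be used". No other stratification factor and no block size is given.

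On the analysis, the Statistical Analysis Plan part of section 2.11 sets its purpose as "To examine changes in outcomes from baseline to the end of the intervention period" and says that "a multivariate repeated-measures mixed-effects regression model will be applied". It then lists the terms: "Participant ID will be included as a random effect", and "group (intervention vs. comparator) and time (T0 vs. T1) will be included as fixed effects". Neither site nor a group-by-time term is listed.

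On expected differences between sites, section 2.6 notes that usual care differs between the countries. The Operational Considerations part of the Discussion adds that "differences in site logistics, staffing, and local clinical practices may influence recruitment rates and adherence".

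On the number of strata, section 2.2 names five centres, two of them in Denmark. Section 2.7 speaks of 4 sites, section 2.9 counts recruitment by country, and section 2.5 keeps the envelopes locally at each site.

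**The concern.** When allocation is balanced within sites, differences in level between sites do not contribute to the true error of the arm comparison. A model that leaves site out may still count that variation as error. The reported standard error is then larger than the design delivers: conservative, and not biased, but wasteful.

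In a pilot, variance estimates matter in their own right. Section 2.9 gives preliminary estimates of variability for the definitive trial as an aim. If between-country variance is not separated out, it can enter the SD used for that calculation. Whether either problem arises depends on the contrast and on the kind of site effect, so each case has to be worked through.

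**Working it through.** **Inputs from the protocol.** Section 2.9: 12 per arm per country in 4 countries, so 12 × 2 × 4 = 96, which reproduces the stated total; 48 per arm. Measurements at T0 and T1. Section 2.7: 85% retention is regarded as acceptable, so 15% missing at T1 is used as one scenario.

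**Assumptions.** The protocol gives no SD, site variance or T0–T1 correlation. Total SD is set to 1, the correlation ρ to 0.5, 0.7 or 0.85, and the share of total variance due to a time-constant site effect f to 0.05, 0.10 or 0.20. Variance of site-specific change, g, is 0.02 or 0.05 of total variance. Arms are balanced within site.

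**1. Arm difference in change, site effect constant over time.** The site effect is the same at T0 and T1, so it drops out of each participant's change and is absorbed by the participant intercept.
- SE = √[(2/48) × 2(1 − ρ)]. At ρ = 0.7: √(0.04167 × 0.6) = 0.158, with or without site. The ratio is 1.00 for every f.
- With 15% missing at T1, simulated mean SEs without and with site are 0.1691 and 0.1689 (f = 0.10), and 0.1668 and 0.1664 (f = 0.20).

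**2. Arm difference in change, change differing by site.** Ratio of the SE without site-by-time to the SE with it = √{[2(1 − ρ) + g] / [2(1 − ρ)]}.
- Smallest: ρ = 0.5, g = 0.02: √(1.02/1.00) = 1.010.
- Largest: ρ = 0.85, g = 0.05: √(0.35/0.30) = 1.080.
- A site main effect alone does not recover this. In simulation with ρ = 0.7 and g = 0.02, the mean SE is 0.1620 without site, 0.1620 with a site main effect, and 0.1583 with site-by-time.

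**3. Group main effect of the listed terms.** This coefficient averages T0 and T1. SE without site = √[(2/48)(1 + ρ)/2]; with site = √{(2/48)[(1 + ρ)/2 − f]}.
- At ρ = 0.7, f = 0.10: √(0.04167 × 0.85) = 0.1882 against √(0.04167 × 0.75) = 0.1768, ratio 1.065.
- Over the three values of ρ:

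| f | Ratio of SEs |
|---|---|
| 0.05 | 1.028–1.035 |
| 0.10 | 1.059–1.074 |
| 0.20 | 1.130–1.168 |

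**4. Baseline means constrained equal between arms.** By simulation at ρ = 0.7 with complete data, mean SEs without and with site are 0.1462 and 0.1454 (f = 0.05), and 0.1467 and 0.1433 (f = 0.20). The ratios are 1.0055 and 1.0237, so about 0.6–2.4%.

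The simulations fit random-intercept models by REML to trials of 96 in 4 strata, with 40 replicates per scenario. That is enough for mean model-based SEs; the empirical SDs are too noisy to use.

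**5. Variance carried forward.** A time-constant site effect goes into the participant-intercept variance, and site-specific change goes into the residual. A total SD (intercept plus residual) therefore contains both unless site and site-by-time are fitted. An SD of change contains only the second.

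**The case against.** The strongest objection is that the section sets out to study change, and for change a constant site effect costs nothing. That stands, and it is the main limit on this point.

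A reader might infer that the SE is too large whichever contrast is used, by 1/√(1 − f): 2.6%, 5.4% or 11.8% for f = 0.05, 0.10 or 0.20, with a future sample size inflated by 1/(1 − f) − 1, about 5–25%. The documents do not support that. The formula fits a baseline-adjusted analysis in which f is site's share of the T1 variance given baseline. The stated model is a repeated-measures model with a participant effect. Nor does a constant site effect enter that model's residual.

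Other objections stand in part. The protocol expects site to affect recruitment and adherence and does not say that it affects change in the 30STS; common training, a shared prescription framework and a test manual work against such differences. Still, adherence acts during the intervention, so a site difference in change is plausible. With no block size given, balance within site is also an assumption: under unblocked lists, omitting site would lose precision and would not overstate the SE. Country-level analyses, which sections 2.9 and the Discussion allow, could supply within-country SDs.

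Finally, a fuller analysis plan may include site. But the article itself names the random and fixed effects under an analysis-plan heading, so the published specification should match the design.

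**Conclusion.** The point holds in a limited form. The stated model does not reflect the only stratification factor. For the arm difference in change with a time-constant site effect, the omission costs nothing.

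The reported SE is too large by about 1–8% if change differs by site (assumed 2–5% of total variance), by about 3–17% if the group main effect is tested (assumed site share 5–20%), or by about 0.6–2.4% if baselines are constrained equal. All three figures assume arms balanced within site and rest on variance shares that the protocol does not give. The error is conservative, and with balanced arms and complete data the point estimate is unchanged.

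Severity is low: this is a pilot without a power calculation, and its Discussion says that it is not powered for efficacy. The practical interest lies in the variance estimates for the next trial and in an unambiguous definition of the strata.

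**What to change.** - Add site as a fixed effect, coded exactly as the strata of the randomisation lists, together with site-by-time in the repeated-measures model. A baseline-adjusted ANCOVA with site is an alternative.
- State that the arm effect is read from the group-by-time contrast, and list that term.
- Report the variance components for the definitive trial from the model with site and site-by-time, so that between-country variance is shown separately.
- Before the lists are generated, state whether the two Danish hospitals are one stratum or two, and align sections 2.2, 2.5 and 2.7. Section 2.14 says that recruitment has not begun, so there may still be time.

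The cost is wording and a few degrees of freedom. With four strata, site and site-by-time take 3 + 3 = 6; with five, 4 + 4 = 8. For the contrast in change with complete data, residual degrees of freedom fall from 96 − 2 = 94 to 94 − 3 = 91 or 94 − 4 = 90.
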